#### Potential confounders at the cluster level

Potential confounders at the cluster level: phase of ART services (stand-alone ART provision vs. any other phase) measured at baseline and number of PALM PLUS training sessions at health centre (< 10 (i.e. less than maximum expected number of trainings) vs ≥10 training sessions, determined at the end of the intervention period. Number of training sessions will not be included in our primary analysis, but only in a secondary analysis as it is a post-randomization variable. *Potential confounders at the individual level: *Age, gender, staff cadre (clinical officer, nurse, medical assistant), staff grade (professional vs. technical), years working in profession, born in Zomba region (yes/no), number of PALM PLUS training sessions attended, and exposure to other MoH trainings (number of days of training); the latter two confounders will be determined at the end of the intervention period.

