### Method of randomization

Health centres will be randomized to the intervention (PALM PLUS) or the control arm (see Figure 1). Random allocations will be generated by the random selection option in the Minitab software program. Randomization will be done using two strata with two levels each. Prior to randomization, health centers will be stratified according to funding source (government funded, n = 15; vs. mission or institutionally funded, n = 15); and health centre size as defined by the number of health centre clinical staff postings defined as doctor, nurse, clinical officer or medical assistant working in the clinic at baseline (levels defined as < median number of HCW for all health centers or ≥median number). All health centers are under the supervision of the Ministry of Health's (MoH) District Health Office (DHO), submit performance data to the DHO, and all staff receive standard MoH training and supervision. This stratification is chosen because there may be subtle management, organizational, and motivation differences in government vs. mission/institutionally funded clinics, and larger staff numbers is a proxy for greater complexity of clinical programming and resources, as well as to ensure balance in terms of numbers of HCWs in both study arms. Randomization within strata will be restricted to ensure equal balance in intervention and control sites by health centre type.

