### Ascertainment of outcomes

Outcomes will be ascertained at baseline and during monthly visits to all health centers; main comparison will be at 12 months vs. baseline;. The clinical manager will be interviewed each visit to determine ongoing employment, and dates of new arrivals and departures of clinical staff. A validated staff satisfaction survey [8] will be administered to clinical staff (at baseline, 2-4 months [for immediate staff satisfaction/retention evaluation], and 10-12 months [late outcomes], ensuring that data is collected for approximately the same calendar months at study and control sites. Patient outcomes will be determined by monthly review of health centre registers and/or patient treatment cards.

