#### Sample size Calculations

At a two-sided alpha of 0.05 and holding power at 80%, using an estimated value for the intracluster correlation coefficient (ICC) of 0.15, and p1 of 0.90 and p2 of 0.65, an inflation factor of 0.15 and an average cluster size of 5 workers then 67 workers will be required per study arm (the sample size unadjusted for clustering is 42 workers). Inflating this by 10% to ensure a sufficient number of staff have completed multiple longitudinal satisfaction surveys within the same health center, brings the required sample to 74 workers which is equivalent to needing 15 clusters (health centers) per study arm. Rationale for ICC: The ICC is almost always unknown prior to conducting a study. In this instance we have chosen an estimate for the ICC to be 0.15. The rationale for the selection of this ICC value is that previous studies have shown higher ICC values for process variables (e.g., health worker days) compared to outcome variables in the primary care setting [9] and in a previous study which summarized the median ICC from several studies using process variables, the median was found to be 0.2 [10].

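### The two stratification factors enter no stated model, and the form in which the baseline outcome is used is left open

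*Protocol article*

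**What the plan says.** **Design.** Under Method of randomization, "health centers will be stratified according to funding source (government funded, n = 15; vs. mission or institutionally funded, n = 15"), and also by centre size, split at the median number of clinical staff at baseline. The reasons given are possible differences in management and motivation between funding types, staff numbers as a marker of clinical complexity, and balance in worker numbers between arms. Allocation within strata is restricted to keep the arms equal.

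**Models.** The Analysis plan adjusts its regression and Cox models for potential confounders, and the section that follows names them. At centre level it reads "Potential confounders at the cluster level: phase of ART services (stand-alone ART provision vs. any other phase) measured at baseline", plus the number of training sessions, which is excluded from the primary analysis. The individual-level list has age, gender, cadre, grade, years in the profession, birthplace and two measures of training exposure. Funding source, centre size and the baseline value of the outcome are in neither list, and no other section places them in a model.

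**Baseline.** Under Ascertainment of outcomes, "Outcomes will be ascertained at baseline and during monthly visits to all health centers", and the main comparison sets 12 months against baseline. The individual satisfaction analysis admits only workers with a baseline survey. Whether baseline enters as a change score, a covariate or in some other way is not said.

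**The concern.** Balancing the arms on a factor removes its contribution from the difference between arms. If the model then omits that factor, the between-stratum variance stays in the residual. The estimated standard error is too large, intervals are too wide, and the test rejects less often than its nominal level. With 30 centres there is little precision to spare.

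The second part concerns outcomes that have a baseline value. Total staffing, a primary outcome, is the clearest case: centres are stratified on baseline staff number, yet that number is not a listed covariate in the model for later staff number. A median split balances size only coarsely, so differences within each half remain.

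**Working it through.** **1. The plan's own figure.** Inputs from Sample size Calculations: "At a two-sided alpha of 0.05 and holding power at 80" per cent, "using an estimated value for the intracluster correlation coefficient (ICC) of 0.15", "p1 of 0.90 and p2 of 0.65", and 5 workers per centre.

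- Pooled-variance formula, mean proportion 0.775: n = (1.96·√(2·0.775·0.225) + 0.842·√(0.09 + 0.2275))² / 0.25² = 42.6; the article gives 42.
- Design effect 1 + (5 − 1)·0.15 = 1.60, and 42 × 1.60 = 67.2. The article: "average cluster size of 5 workers then 67 workers will be required per study arm (the sample size unadjusted for clustering is 42 workers").
- 67 × 1.10 = 73.7 and 74 / 5 = 14.8. The article: "brings the required sample to 74 workers which is equivalent to needing 15 clusters (health centers) per study arm".

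The figure reproduces. It does not depend on the adjustment set, so no new sample size follows. What changes is the precision obtained from 15 centres per arm.

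**2. Strata.** Let R² be the share of between-centre outcome variance that the two factors explain. The article gives no value, so 0 to 0.4 is assumed. With strata balanced, the true variance of the arm difference is about (1 − R²) times the variance that an unadjusted model estimates. At R² = 0.2 the standard error is overstated by about 1/√0.8 = 1.12.

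Simulation: 20,000 trials per cell, 30 centres in four strata of assumed sizes 8, 7, 8 and 7, allocation balanced within strata, and a linear model with and without the two factors. The effect is set to give 80% power in an unadjusted t test on 28 degrees of freedom when R² = 0.

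| Assumed R² | Type I error, strata omitted | Type I error, strata included | Power, strata omitted | Power, strata included |
|---|---|---|---|---|
| 0 | 4.8% | 4.8% | 80% | 79% |
| 0.1 | 3.7% | 4.9% | 81% | 84% |
| 0.2 | 3.0% | 5.2% | 82% | 87% |
| 0.3 | 2.1% | 5.1% | 83% | 92% |
| 0.4 | 1.4% | 5.2% | 85% | 95% |

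At R² = 0 the unrounded powers are 80.0% and 79.5%, a cost of about half a point.

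**3. Baseline value.** Let r be the correlation between the baseline and 12-month centre values, also not given and assumed to lie between 0.3 and 0.8. Relative to a follow-up-only analysis (variance 1), a change score has variance 2(1 − r) and covariate adjustment has 1 − r². Their ratio is (1 − r²) / (2(1 − r)) = (1 + r)/2. Power is on the same scale, where follow-up only has 80%.

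| Assumed r | Change score | Covariate | Covariate ÷ change score | Power, change score | Power, covariate |
|---|---|---|---|---|---|
| 0.3 | 1.40 | 0.91 | 0.65 | 66% | 84% |
| 0.5 | 1.00 | 0.75 | 0.75 | 80% | 90% |
| 0.7 | 0.60 | 0.51 | 0.85 | 95% | 98% |
| 0.8 | 0.40 | 0.36 | 0.90 | 99% | >99% |

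Below r = 0.5 a change score is less precise than ignoring baseline. Covariate adjustment is never less efficient than either alternative, apart from the one degree of freedom it uses.

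**The case against.** The best case for the plan has four parts.

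- **The list may not be the whole model.** It is headed as confounders, which is not what design factors and baseline outcomes are usually called, and a condensed article may leave the rest to an analysis plan. This carries weight for the form of the baseline comparison. It carries less for the strata: the article goes into enough detail to name its covariates and to bar one from the primary analysis, yet the two factors that restrict allocation are absent.
- **Baseline is not ignored.** A reader might infer from the lists that baseline data are thrown away, or that centres are compared with no regard to size. The article does not support that. It names a comparison with baseline, requires a baseline survey for the individual satisfaction analysis, and divides treatment initiations by referral population. The size concern is therefore confined mainly to total staffing and to counts without a stated denominator, such as total patient visits. Nor does the point reach every outcome, because retention has no baseline value.
- **The gain can be overstated.** At r = 0.7, 1/0.51 = 1.96 suggests that adjustment is worth a doubling of the centres. That holds only against an analysis that ignores baseline. Against a change score the figure is 1/0.85 = 1.18, or about 18% more centres.
- **The error is on the safe side.** Omitting the strata is conservative, and power without them stays between 80% and 85% in the simulation. This is right, and it rules out a claim of bias or that the omission settles the trial's result. Intervals that are too wide are still a fault when the remedy costs so little.

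**Conclusion.** The point stands in two parts of unequal strength.

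The strata part is firm: the article restricts randomization on two factors and puts neither in any stated model. The consequence is lost precision, not bias. At an assumed R² of 0.1 to 0.2, inclusion adds about 3 to 5 points of power and brings the type I error back from 3.0–3.7% to about 5%.

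The baseline part is a matter of specification: the form is open, and for satisfaction, total staffing and the register-based outcomes the covariate form is the efficient choice. Its size depends on r and on which alternative was meant.

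R², r and the stratum sizes are assumptions. The figures apply to centre-level linear models and do not carry over directly to the Cox or log-link binomial models. This should be corrected, but it does not threaten the trial's validity.

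**What to change.** - Include funding source and baseline centre size in the primary arm comparisons. For retention, add these two factors only.
- In the linear models for satisfaction, total staffing and register-based outcomes, state that the baseline value of the outcome enters as a covariate.
- Keep ART phase as a pre-specified covariate.
- In the Cox and log-link binomial GEE models, limit the added terms to the two stratification factors, and name a fallback in case a model does not converge.
- Settle the wording before outcome data by arm are seen.

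**Cost.** Wording only; the data are already collected. In a centre-level model the two strata terms and the baseline value use about 3 of the 28 degrees of freedom (30 centres less intercept and arm). ART phase uses one more, but the plan already includes it.

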Trainers will be expected to lead between 6 to 10 training sessions at each health centre, targeting all nursing and clinical staff working at the health centre, over a maximum period of 12 weeks, but they may conduct additional training sessions if they wish. Point-of-care guideline tools will be developed and distributed (e.g a thin (about 30 pages) sturdy laminated ring binder containing the entire guideline, colourful and easy to follow algorithms designed to be on the primary care provider's desktop during each patient encounter, as well desk blotters with key PALM PLUS messages.

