### Control sites

No PALM PLUS materials or training will be provided to personnel working at control health centers. Routine ongoing health centre supervision by District Health Office (DHO) personnel and off-site DHO training courses will continue in all sites.

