#### Analysis plan

In cluster randomized controlled trials with relatively few clusters, it is recommended to assess the effectiveness of randomization as a first step. Therefore, we will first examine the balance of baseline characteristics of the health centre clusters and the individual patients across intervention groups. Analyses will be done at both cluster (health centre) and individual (health care worker) levels, adjusted for clustering. At the health centre level (cluster level), we will use multivariable linear regression to compare mean staff satisfaction, staff retention and total staffing, adjusting for potential confounders. At the health worker level (individual level), multivariable regression adjusted for clustering by health centre will be used to compare HCW satisfaction scores. For this analysis, we will only include those HCWs who complete a survey at baseline and the appropriate outcome time point and are working in the same health center. Cox regression modeling will be used to estimate the survival probabilities of health care workers (proportion of days employed at health centre over two years of follow-up) to compare 'survival' (sustained days of work at same health centre) across intervention groups, adjusting for potential confounders. Health centre level analyses will use multivariable linear regression to compare secondary outcomes such treatment initiation (ARV, cotrimoxazole, TB, malaria etc.). Treatment initiation will be calculated as the number of patients placed on "X" treatment over the denominator of "Y" health centre referral population. To adjust for cluster randomization, we will use generalized estimating equation binomial regression models with log link and exchangeable correlation structures to estimate the relative risks (RR) and 95% confidence intervals for 'survival' rates (proportion of days employed at health centre over two years of follow-up) between the intervention group (receive PALM PLUS) with the control group as a reference. SAS version 9.2 (SAS Institute Inc, 2008) will be used for all analyses. All analyses will be conducted using the intention to treat principle.

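### Two individual-level covariates measured after randomisation, one of them the dose of the intervention itself, lack the exclusion that the plan gives to the cluster-level session count

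*Protocol article*

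**What the plan says.** All the covariate lists stand under the heading Potential confounders at the cluster level.

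- **Cluster list.** It contains phase of ART services and "number of PALM PLUS training sessions at health centre (< 10 (i.e. less than maximum expected number of trainings) vs ≥10 training sessions". Directly after comes the only exclusion: "Number of training sessions will not be included in our primary analysis, but only in a secondary analysis as it is a post-randomization variable".
- **Individual list.** This follows the exclusion. After age, gender, cadre, grade, years in profession and birthplace it adds "number of PALM PLUS training sessions attended, and exposure to other MoH trainings (number of days of training", and then states that "the latter two confounders will be determined at the end of the intervention period". No restriction to secondary analysis is attached.

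The Analysis plan section sets out the models. Cox regression compares "survival' (sustained days of work at same health centre) across intervention groups, adjusting for potential confounders". For satisfaction at worker level, "multivariable regression adjusted for clustering by health centre will be used to compare HCW satisfaction scores"; that sentence names no covariates. The section ends by placing all analyses under intention to treat. Outcome measures names retention and satisfaction as primary.

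On exposure, Control sites says "No PALM PLUS materials or training will be provided to personnel working at control health centers". In the intervention arm, "Trainers will be expected to lead between 6 to 10 training sessions at each health centre", over at most 12 weeks.

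**The concern.** A confounder of a randomised comparison is a baseline variable that happens to be unbalanced. Sessions attended is not of that kind. It is caused by allocation, it is the amount of intervention received, and it is zero throughout the control arm. With it in the model, the arm coefficient no longer measures the effect of being allocated to PALM PLUS. It measures the effect of allocation for a worker who attended nothing, a value extrapolated from the few intervention workers near zero.

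The article gives this very reason for holding back the cluster-level count, and the reason applies equally to both individual-level variables. If an analyst follows the individual list literally, the worker-level results on primary outcomes could lose a real effect or, for retention, show an effect of the wrong sign.

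**Working it through.** The plan gives no figure for this point, and no sample-size figure depends on it. The check has a textual part and an illustrative numerical part.

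**1. Text side by side**

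| Variable | When measured | Value in controls | Exclusion from primary analysis |
|---|---|---|---|
| Sessions held at the centre | end of intervention period | 0, so always below 10 | stated |
| Sessions attended by the worker | end of intervention period | 0 | not stated |
| Days of other MoH training | end of intervention period | above 0 possible; routine training continues in all sites | not stated |

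**2. Loss of precision for the arm coefficient**

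Inputs: equal arms and zero sessions in controls (Control sites). The mean m and SD s of sessions attended in the intervention arm are assumptions, guided by the 6 to 10 sessions per centre in The Intervention.

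- Between-arm variance of sessions: m²/4
- Average within-arm variance: s²/2, since the control variance is 0
- R² = between/(between + within); VIF = 1/(1 − R²); SE factor = √VIF

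| m, s (assumed) | Between | Within | R² | VIF | SE factor |
|---|---|---|---|---|---|
| 8, 1.4 | 16 | 0.98 | 0.94 | 17.3 | 4.2 |
| 6, 2.5 | 9 | 3.125 | 0.74 | 3.9 | 2.0 |
| 5, 3 | 6.25 | 4.5 | 0.58 | 2.4 | 1.5 |

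**3. What the arm coefficient estimates (satisfaction)**

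If total effect = direct part + (effect per session × mean sessions), a linear model with sessions included returns only the direct part.

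Simulation inputs: 30 centres of 5 workers and ICC 0.15 (Sample size Calculations), 6 to 10 sessions per centre. Assumed: 80% attendance and a total effect of 0.50 SD.

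| Share of effect through sessions | Arm coefficient without sessions (empirical SE) | With sessions (empirical SE) | SE ratio |
|---|---|---|---|
| all | 0.50 (0.214) | 0.00 (0.595) | 2.8 |
| half | 0.50 (0.209) | 0.24 (0.598) | 2.9 |
| none | 0.50 (0.206) | 0.50 (0.566) | 2.7 |

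Even when nothing runs through sessions, the precision is lost.

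**4. Retention (Cox)**

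A worker who leaves during the training period stops accumulating sessions. Within the intervention arm, low attendance then predicts leaving because leaving caused it. The model credits sessions with a protective effect, and the arm term, evaluated at zero sessions, is pushed upward.

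Illustration, with 30 centres of 5 workers and the proportions 0.65 and 0.90 from Sample size Calculations. Assumed: these are 12-month retention with 0.65 in controls, 6 to 10 sessions spread over 12 weeks, 80% attendance, a centre-level frailty and model-based standard errors.

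- No true effect: median hazard ratio 0.97 without sessions and 8.7 with sessions; false harm was significant in 74% of runs.
- True hazard ratio ln 0.90/ln 0.65 = 0.105/0.431 = 0.24: the adjusted median was 2.1. Significant benefit was found in 3% of runs, against 93% without sessions.

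A repeat with no true effect and a log-normal centre effect of SD 0.4 gave 0.98 without and 7.6 with sessions. The size moves with the assumptions, but the direction did not change.

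**5. MoH training days**

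In the step 3 simulation, adding MoH days generated independently of arm and outcome left the arm coefficient at 0.50. Bias needs a link: PALM PLUS changing uptake of other training, or, in the Cox model, early leavers accumulating fewer days.

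**The case against.** Several points on the other side have force.

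- **The exclusion may already cover sessions attended.** The sentence names no level, and intention to treat is declared for everything. But it stands directly after the cluster variable and before the individual list, and on no reading does it reach MoH training days. The ambiguity remains.
- **Not every model is shown to be affected.** Only the Cox model, among worker-level analyses, is expressly adjusted for potential confounders. The satisfaction sentence names no covariates, nor does the log-binomial GEE for retention. The centre-level regressions draw on a list from which sessions are excluded. So retention and satisfaction each keep at least one untouched analysis. This limits the damage but does not justify the list.
- **The figures rest on assumptions.** This stands. The article gives no attendance distribution, and the SE factor runs from 1.5 to 4.2.

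A reader might infer three stronger things that the article does not support. The first is that adjustment sends the arm effect to zero: that needs the whole effect to be carried by sessions, whereas guideline binders and desk blotters are supplied as well. The second is that the bias is always toward no effect: for retention it can pass the null. The third is that MoH days certainly bias the result: routine MoH training continues in both arms, and no text suggests that PALM PLUS alters its uptake.

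**Conclusion.** The point holds in this form: the article lists two end-of-intervention variables as individual-level confounders without the restriction that it rightly gives the cluster-level count, and so permits worker-level comparisons on primary outcomes to condition on the intervention's dose. That conflicts with the stated intention-to-treat principle.

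For satisfaction, the part of the effect running through sessions would be removed and the standard error inflated about 1.5 to 4 times, given assumed attendance. For retention, truncation by leaving can distort the arm effect in either direction, including toward false harm; it acts on sessions mainly through staff who leave within the training period of up to 12 weeks. For MoH days the bias is possible, not shown. The textual defect needs none of the assumed figures.

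The centre-level analysis of sessions (below 10 against 10 or more) could look like the same error, since all controls fall below 10. It is already labelled secondary and post-randomisation, so it need not change.

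**What to change.** Extend the existing exclusion sentence so that it also names, at individual level, PALM PLUS sessions attended and days of other MoH training. State that primary arm comparisons, including the Cox retention model and the worker-level satisfaction model, adjust only for variables measured at or before randomisation. Keep the two variables for secondary or exploratory description: sessions attended within the intervention arm, and MoH training days tabulated by arm.

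The cost is a change of wording in the analysis plan. No new data are needed, and neither the sample size nor the data collection changes.
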